The epidemiological cycle of *T. solium* occurs mostly in environments with low socio-economic or low hygiene levels, deficient sanitary facilities, or poor pig rearing practices where pigs can gain access to human faeces. Cysticercosis is most common in developing countries of Latin America, Asia, and Africa (Plancarte *et al.,* 1999). However, due to migration of people and tourism, human cysticercosis is now transmitted world-wide and it is considered as an emerging disease in the United States of America (Flisser *et al.,* 1998). Human cysticercosis has been reported in non pork-consuming communities such as the orthodox community in the USA (Schantz *et al.,* 1992). Studies on *T. solium* infections in Tanzania have largely been based on the infections in pigs, however, the possible medical implication of the parasite has been suggested by the presence of hospital records of human epilepsy and taeniosis in the studied areas ([name], 1999; Boa, unpublished report). A study conducted at household level in 21 randomly selected villages in Mbulu district northern Tanzania, established an overall prevalence of 17.4% (range 3.2-46.7%) of porcine cysticercosis in 770 live pigs examined by lingual examination ([name], 1999). This prevalence is higher than those reported by some similar studies in other highly endemic regions of the world. For example in Nigeria 5.5% of 1 300 pigs examined were found to be infected (Onah and Chiejina, 1995) while in Mexico, a prevalence of 4% was reported in 571 live pigs examined (Sarti *et al.,* 1992). Mbulu district was found to have a high potential for the spread of *T. solium* infections due to identified transmission factors. Out of 425 households observed, 21.6% did not have latrines. Of 198 respondents to interviews, 94.4% allowed their pigs to roam for food, and 41% of the respondents lacked knowledge on how a pig could acquire cysticercosis ([name], 1999). Thus, public health education could contribute in reducing the risk of this severe disease. Several studies have found that neither age nor sex of the pig had a significant association with the prevalence of porcine cysticercosis (Sarti *et al.*, 1992; Onah and Chiejina, 1995; Sakai *et al.*, 1998; [name], 1999). Studies in young pigs have indicated that infection rates are significantly higher in dry than in wet season (De-Aluja *et al.*, 1998; [name], in process). In the study in Mbulu, this was linked to the fact that during dry season pigs are let free to look for food in the fields since at this time crops have been harvested. On the other hand during wet season pigs are housed or tethered to restrict them from destroying crops in the fields. Seasonal prevalence of porcine cysticercosis should be considered when targeting and evaluating control measures.

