**Study population**

Sample size calculation:

Although the village will be the unit of intervention allocation, the main analysis will be based on individuals since from previous study there was little variation in the prevalence of porcine cysticercosis in different villages (coefficient of variation was about 0.1). Therefore the sample size has been calculated using the formula,

n = [(z1 + z2)2 2P (1-P)]/(p1 – p2)2.

In the formula, n is number of pigs required in each group, z1 is the z score for the specified confidence level, and z2 is the z score for the specified power. p1 and p2 are the prevalence of the disease in the intervention and control group respectively, and p1 and p2 P is the average of p1 and p2 (Smith and Morrow, 1996).

The sample size is calculated based on the prevalence of porcine cysticercosis as the main outcome measure. The prevalence of porcine cysticercosis in the area was estimated to be 14.64% adjusted for various confounders ([name], 1999). We would like the present study to have 80% power to detect a significant difference with 95% confidence if the intervention will reduce the prevalence of porcine cysticercosis by 30%. The number of villages required in each group is therefore calculated to be:

n = [(1.96 + 0.84) 2 2 x 0.1244 (1-0.1244)]/(0.1464-0.1023)2

= 878.20.

Approximately 900 pigs will be examined in each of the two groups. A total of 1800 pigs will be examined before intervention and 1800 after intervention.

Selection of villages and study participants:

The number of villages to be included in the study will depend on the number of pig farmers available in the villages. This information will be obtained in the pilot study. All pig farmers in the selected villages will be enrolled in the study.

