##### Data collection methods and experimental procedure

##### Pre-intervention examination of the study population:

A structured questionnaire will be used to collect demographic data of all the study participants. In-depth interviews of five farmers in each village will be done to study human perceptions of the disease. Structured observations will be done in all selected households to study practices related to the transmission of the disease such as pig rearing practices, use and status of latrine, boiling of water for drinking, washing hands before eating and after using a latrine, and eating of infected pig meat.

All pigs in the household will be examined by the researcher using lingual palpation and blood samples collected for antigen ELISA.

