**Statistical analysis**

Due to the fact that pigs will be clustered in households that are also clustered in villages and climates, a hierarchical logistic regression model will be used to analyse the data in order to take care of different levels of clustering and possible interactions. The effectiveness of intervention in improving human perceptions and practices will be computed by comparing average scores in the two groups adjusted for baseline values. Change in the prevalence of porcine cysticercosis will be computed and adjusted for important confounders such as age, sex of the pig, and other important household characteristics that might affect the prevalence of the disease. Seasonal prevalence of porcine cysticercosis will be taken into considerations when evaluating the intervention.

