**Study limitations**

Due to the short period available for the data collection (about two years), it might not be possible to observe significant reduction in the disease prevalence. However, improvement in perceptions and practices related to the transmission of the disease will be used as intermediate outcomes to indicate reduction in the transmission of the disease.

Maternal antibodies due against porcine cysticercosis have been reported to persist beyond nine months of pig’s life. This may limit the use of ELISA or immunoblot tests that have been reported to respond on these antibodies. This is because we would like to detect actual cases (and not false positives due to maternal antibodies) and to be able to disentangle cases hat occured before and those that occurred after the intervention. Most studies on antigen ELISA for porcine cysticercosis are still under trial and some have reported that antigens are detected up to 200 days post-infection and tend to disappear afterwards probably due to formation of immune complexes.

We are not sure that we will get enough pigs for post-intervention study since we don’t know how prolific are the pigs in the study area. From the previous study, one farmer in Mbulu had an average of 1.8 pigs. Our aim is to examine a different population of pigs in the post-intervention from the pre-intervention study. This is because in this particular disease we cannot know the onset of the infection, otherwise we could include the pre-intervention population that had not been infected in the post-intervention study.

Due to the fact that the intervention is information based, leaking of information from intervention to the control group might be a problem. However care will be taken to have a clear geographical separation of the groups. In addition, participants in the control group will be assured well in advance that they will receive the intervention after the study in order to minimise chances of them seeking information from the intervention group. The researcher will investigate if there is any leakage of information from the intervention to the control group, or if there is any change in hygiene policy during the study period in order to take care of these during data analysis. [In this point I am still thinking if we can use blinding which is known to reduce bias]

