**Dissemination of research results**

Findings from this research will be disseminated to various relevant parts. The community feedback will be through organising workshops and seminar with the study population. Written reports will be given to the district and village authorities. A thesis will be produced and a copy will be available in the institutional library. Scientific papers will be written and published in relevant journals. Oral or poster presentations will also be given in relevant scientific conferences and workshops.

BUDGET

| **Requirement** | Cost | |
| --- | --- | --- |
| TAS | **US $*** |
| *Equipments* |  |  |
| A video system (deck + screen) | 600 000 | 750 |
| An electric generator to drive the video in the villages | 300 000 | 375 |
| Tape recorder & 10 cassettes for questionnaire recording | 220 000 | 275 |
| 1 pig snare for restraining the pig during examination | 100 000 | 125 |
| **Sub-total** | **1 220 000** | **1 525** |
| *Materials* |  |  |
| 1videotape production | 19 000 000 | 23 750 |
| 1 000 brochures | 700 000 | 250 |
| 1 000 forms for farmers to keep records | 100 000 | 125 |
| Travels associated with media production | 300 000 | 375 |
| 100 m of a cotton material @ 1000/= for holding pig’s tongue during examination | 100 000 | 125 |
| **Sub-total** | **20 200 000** | **25 250** |
| *Allowances and accommodation* |  |  |
| 15 months of data collection in Mbulu:   - - - Per diem for 3 (researcher, driver, technician) people @ 14 000/day     - Anthropologist to assist on anthropological data collection (allowance to be negotiated)     - Accommodation: 8 000/person/day | 18 900 000  10 800 000 | 23 625  13 500 |
| **Sub-total** | **29 700 000** | **37 125** |
| *Local travel costs for the 15 months* |  |  |
| [Morogoro – Arusha-Mbulu (800 km) + return] x 15 months x 700/= / 8 km  Within Mbulu 50 km/day (estimated)  Vehicle maintenance (10% fuel cost) | 2 100 000  3 543 750  564 375 | 2 625  4 429.69  7 054.69 |
| **Sub-total** | **6 208 125** | **7 760.16** |
| *Overseas travel costs* |  |  |
| Research methodology course (4.5 months)  -return air ticket to Denmark  -subsistence allowance 480 000/= per month  Thesis write up (9 months)  - return air ticket to Denmark  -subsistence allowance 480 000/= per month | 1 563 200  2 160 000  1 563 200  4 320 000 | 1 954  2 700  1 954  5 400 |
| **Sub-total** | **9 606 400** | **12 008** |
| *Other costs* |  |  |
| Fuel for running the generator | 20 000 | 25 |

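### Post-intervention visits are not balanced by arm over the calendar, so season can differ between arms and is left to later adjustment

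*Protocol*

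**What the plan says.** The Introduction states that in young pigs "infection rates are significantly higher in dry than in wet season". It links this in Mbulu to pigs being released after harvest and confined while crops stand, and concludes that season matters both for targeting and for evaluating control measures. Study area places the rains in March to mid-May and in November to December.

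On workload, Study population says "A total of 1800 pigs will be examined before intervention and 1800 after intervention", and the pre-intervention section says "All pigs in the household will be examined by the researcher using lingual palpation". The post-intervention section keeps similar methods but restricts the examination to pigs born since the education. The Budget provides for "15 months of data collection in Mbulu" without dividing this among rounds.

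Villages are randomised after the baseline survey, within groups of similar baseline prevalence (Allocation of villages to intervention). To limit leakage of information, Study limitations adds: "However care will be taken to have a clear geographical separation of the groups". No section names survey months, sets the order in which villages are visited, or balances that order by arm. Season returns only under Statistical analysis: "Seasonal prevalence of porcine cysticercosis will be taken into considerations when evaluating the intervention". The same section plans a hierarchical logistic model with adjustment for confounders.

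**The concern.** The outcome pigs are those in which the protocol expects season to matter, and one examiner cannot see about 1000 households at once. Randomisation balances villages. It does not balance the dates on which they are later visited, because that calendar is drawn up once the arms are known. Two features make an uneven calendar plausible: the arms are to be kept geographically apart, and the education sessions are scheduled around one researcher, while control villages have no session to fix their visit date.

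If control villages are examined more often in the dry season, a seasonal difference looks like a benefit of the education. If intervention villages are, a real benefit is hidden. The visiting order is a field decision. Once the pigs have been examined, the analysis can only adjust for whatever imbalance arose.

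**Working it through.** **The plan's own sample size.** n = (1.96 + 0.84)² × 2 × 0.1244 × (1 − 0.1244) / (0.1464 − 0.1023)² = 878.20 per group, as the protocol prints, rounded to about 900. The target difference is 14.64 − 10.23 = 4.41 percentage points.

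**Length of a round.** Study limitations gives 1.8 pigs per farmer, so 1800 / 1.8 = 1000 households. The daily rate is not stated and is assumed here:

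| Households per day | Field days | Months at 20 working days |
| --- | --- | --- |
| 5 | 200 | 10 |
| 10 | 100 | 5 |
| 20 | 50 | 2.5 (1.7 at 30 days) |

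The range is thus about 2 to 10 months. The longest dry stretch implied by Study area, mid-May to October, is about 5.5 months. A round may or may not cross seasons.

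**Spurious effect without adjustment.** Let r be the dry/wet prevalence ratio (assumed; not in the documents), and let i and c be the shares of intervention and control pigs examined in the dry season. With no true effect, the prevalence ratio is (i·r + 1 − i) / (c·r + 1 − c).

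| Dry-season share, control vs intervention | r = 1.2 | r = 1.5 | r = 2 |
| --- | --- | --- | --- |
| 75% vs 25% | 0.913 (9% lower) | 0.818 (18% lower) | 0.714 (29% lower) |
| 60% vs 40% | 0.964 (4% lower) | 0.923 (8% lower) | 0.875 (13% lower) |

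In percentage points, take a mean prevalence of 14.64% with half of all examinations in each season. Wet prevalence is then 2 × 14.64 / (1 + r). At r = 2 the seasons differ by 19.52 − 9.76 = 9.76 points, so a share difference of 4.41 / 9.76 = 0.45 equals the whole target effect. At r = 1.5 they differ by 17.57 − 11.71 = 5.86 points, and the share difference needed is 0.75.

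**Cost of adjusting afterwards.** Let s be the difference between arms in dry-season share, with half of all examinations in each season. A season term then inflates the variance by 1 / (1 − s²), which leaves 900 × (1 − s²) effective pigs per arm:

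| s | Effective pigs per arm | Power |
| --- | --- | --- |
| 0 | 900 | about 81% |
| 0.2 | 864 | about 79% |
| 0.5 | 675 | about 69% |
| 0.7 | 459 | about 53% |
| 0.9 | 171 | about 23% |
| 1 | 0 | not estimable |

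These figures ignore village clustering, as the protocol's formula does, and are therefore optimistic.

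**If the order is unrelated to arm.** The number of villages is left open. With 5 per arm (assumed) and half of the villages visited in each season, the mean absolute s is 0.29; with 10 it is 0.17 and with 20 it is 0.12. Complete coincidence of season and arm with 5 per arm has probability 2 / 252 = 0.8%.

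**The case against.** The protocol does commit to considering season and plans a model in which it could be a covariate. How season enters that model is ordinary analysis-plan content, and the visiting order is often left to a field manual. Separation of the groups is a measure against leakage and does not say that one arm is surveyed first. Visiting by arm is therefore a possibility, not a stated plan. All of this stands, and it limits the strength of the point. It does not remove it, because an analysis plan cannot restore balance after the fieldwork.

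Four stronger readings are tempting, and the documents do not support them.

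- A reader might infer that a round takes about five months, since 15 budgeted months over three assessments is 5. That is time available, not time needed. The budget block also lists help with anthropological data, and pigs are examined in only two rounds.
- A reader might infer that a round must cross the rains. The survey months are not fixed, and even 150 days fits between mid-May and October.
- A reader might infer that the analysis cannot separate season from arm. This is so only when the two coincide completely. With any overlap, a season term separates them, at a cost in power.
- A reader might infer that the baseline visits could be ordered with the arms known. Allocation follows the baseline survey, so no arms exist then. What remains at baseline is narrower: the prevalence used to group villages may partly reflect the month of the visit.

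One further limit cuts both ways. The Introduction gives 60 to 70 days for larvae to develop, so the date of examination is an imperfect marker of the season of exposure. Adjustment for examination period may leave some confounding. Visiting the arms side by side does not depend on that model.

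**Conclusion.** The point holds as a gap in the post-intervention field design. The protocol reports a seasonal effect in young pigs and examines pigs born after the education through one researcher, yet neither fixes the survey months nor balances the visiting order by arm. If a round spans seasons and the arms are unevenly spread over it, the unadjusted distortion can approach the 30% target: 18% to 29% for a 75% versus 25% split at an assumed ratio of 1.5 to 2, and 4% to 13% for 60% versus 40% at ratios of 1.2 to 2. With adjustment, the loss is mainly one of power: about 81% to 69% at the first split and to 79% at the second, before clustering.

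These sizes rest on the assumed ratio, the assumed splits, and a round that crosses seasons. None of the three is given in the protocol. The change is worth making because it is cheap and cannot be made after fieldwork.

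**What to change.** Add to the post-intervention examination section, for the post-intervention rounds only:

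> Intervention and control villages of the same randomisation group are examined one directly after the other, in random order within the group, in the same calendar period.

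This also gives control villages a date for the reassessment that follows the education. State under Statistical analysis that calendar period (season) of examination enters the hierarchical model.

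At baseline, where no arms exist yet, confine the survey to one season where feasible, or take the survey period into account when villages are grouped by prevalence. I would not require each village to be re-examined in its baseline calendar month. Baseline visits cannot be paired by group, so members of one group may have different baseline months, and that rule could conflict with paired visits.

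The cost is more driving between areas that are meant to be apart, and a fixed field calendar. No extra pigs, staff or visits are needed.

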# In the calculation of economic losses by the farmer it shall be assumed total condemnation of the infected pig. This is the regulation of the government and it is practised by most people in Mbulu district. The prevalence of porcine cysticercosis in all one-year old pigs in the control group will be used to estimate the economic losses by the farmer assuming that the pig is sold at one year of age. The average price of a pig will be estimated using the existing price.

The economic loss will be calculated as the loss in net returns due the disease prevalence + costs incurred due to condemnation of infected pig carcasses.

**Activity time plan**

| **Activity** | **Year 1** | **Year 2** | **Year 3** | **Year 4+** |
| --- | --- | --- | --- | --- |
| Develop research proposal | X |  |  |  |
| Attend Research Methodology course | X |  |  |  |
| Phase 1 (collect anthropological data) |  | X |  |  |
| Attend Applied Epidemiology course |  | X |  |  |
| Phase 2 (produce ed. Materials) |  | X |  |  |
| Phase 3 (evaluate ed. Materials) |  | X | X | X |
| Preliminary data analysis |  |  |  | X |
| Community feedback and evaluation |  |  |  | X |
| Final data analysis and publication |  |  |  | X |

ADDITIONAL CONSIDERATIONS

##### Ethical considerations

The researcher will ask for informed consent from the study participants before she can carry out the study. Confidentiality of the study participants will be adhered to. Ethical clearance will be requested from the National Institute for Medical Research ethical clearance committee in Tanzania. Research permission will also be requested from the researcher’s home institution (Sokoine University of Agriculture, Tanzania). After the end of the study the control group participants will receive the intervention. If the study participant or the family member is ill in our presence, she/he will be carried by the project vehicle to the health centre. If the animal of the study participant is sick the farmer will be advised to seek for the veterinary advice. If the intervention will be found effective it will be considered for the district.

**Study limitations**

Due to the short period available for the data collection (about two years), it might not be possible to observe significant reduction in the disease prevalence. However, improvement in perceptions and practices related to the transmission of the disease will be used as intermediate outcomes to indicate reduction in the transmission of the disease.

Maternal antibodies due against porcine cysticercosis have been reported to persist beyond nine months of pig’s life. This may limit the use of ELISA or immunoblot tests that have been reported to respond on these antibodies. This is because we would like to detect actual cases (and not false positives due to maternal antibodies) and to be able to disentangle cases hat occured before and those that occurred after the intervention. Most studies on antigen ELISA for porcine cysticercosis are still under trial and some have reported that antigens are detected up to 200 days post-infection and tend to disappear afterwards probably due to formation of immune complexes.

We are not sure that we will get enough pigs for post-intervention study since we don’t know how prolific are the pigs in the study area. From the previous study, one farmer in Mbulu had an average of 1.8 pigs. Our aim is to examine a different population of pigs in the post-intervention from the pre-intervention study. This is because in this particular disease we cannot know the onset of the infection, otherwise we could include the pre-intervention population that had not been infected in the post-intervention study.

Due to the fact that the intervention is information based, leaking of information from intervention to the control group might be a problem. However care will be taken to have a clear geographical separation of the groups. In addition, participants in the control group will be assured well in advance that they will receive the intervention after the study in order to minimise chances of them seeking information from the intervention group. The researcher will investigate if there is any leakage of information from the intervention to the control group, or if there is any change in hygiene policy during the study period in order to take care of these during data analysis. [In this point I am still thinking if we can use blinding which is known to reduce bias]

There might be barriers to community change due to the fact that some change in practices such as housing pigs may require additional resources to cater for extra labour and food. The pilot study will investigate the possible barriers and take them into considerations when evaluating the effectiveness of the program.

Currently there is an outbreak of African swine fever in the capital city of Tanzania that has resulted in restriction of pig movements and slaughtering of all infected pigs. It is not known how far this will spread and for how long it will last. This might affect the pig population in Tanzania and might have some impact in the present study.

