# Allocation of villages to intervention:

Two groups will be compared whereby one group will receive the health education while the other group will act as a control. The villages will be grouped according to their similarities in their prevalence of porcine cysticercosis obtained during pre-intervention study and randomised within groups to either control or intervention.

Intervention:

Participants in the control group will follow their usual hygiene and pig management practices. For the intervention group, the educator in each village will organise and conduct two training sessions one- month interval. After the first session the educator will distribute pamphlets to the participants for further reference. The day after the session, the participants in the intervention group will watch a video program. The researcher will participate in the sessions as an audience, therefore the interventions in the selected villages will be planned such that the researcher will participate in all the villages.

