# Post-intervention examination of the study population:

The researcher will reassess perceptions and practices immediately after the intervention and at the end of the study. All pigs born after the intervention will be examined. Similar methods of data collection used in the pre-intervention study will be used in this study. However, the last questionnaire interview will include a question designed to investigate if the participants in the control group have received any information regarding the health education from the intervention group in order to take care for possible confounder during data analysis. The research will also investigate if there has been any change in hygiene policy at any time during the study.

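### A non-significant result on prevalence, the main outcome, may be read as reduced transmission on the strength of perceptions and practices, assessed by a researcher who knows the allocation

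*Protocol*

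**What the plan says.** Protocol, Study population (sample size calculation): "The sample size is calculated based on the prevalence of porcine cysticercosis as the main outcome measure". The target is "80% power to detect a significant difference with 95% confidence" for a 30% relative reduction.

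Protocol, Study limitations: data collection lasts about two years, which may be too short to show a significant fall in prevalence. The next sentence offers the way round this: "improvement in perceptions and practices related to the transmission of the disease will be used as intermediate outcomes to indicate reduction in the transmission".

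On who assesses:
- Protocol, Intervention: "The researcher will participate in the sessions as an audience", and the sessions are scheduled so that this is possible in every intervention village.
- Protocol, Phase one: the same researcher trains the village educators.
- Protocol, Post-intervention examination: "The researcher will reassess perceptions and practices immediately after the intervention and at the end of the study", by methods similar to those of the baseline survey (questionnaire, in-depth interviews, household observation).
- Protocol, Pre-intervention examination: the researcher also palpates the pigs' tongues, and blood is taken for antigen ELISA.

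On blinding, the only text is a bracketed note in Study limitations: "I am still thinking if we can use blinding which is known to reduce bias".

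**The concern.** Listing perceptions and practices as outcomes is not the fault; they are specific objective (iii). The fault is the inference attached to them. When prevalence is not significant, a different set of measures is given the job of showing that transmission has fallen. Prevalence in pigs is what the Summary itself calls a reliable indicator of active transmission, so the fallback replaces the direct measure with indirect ones.

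The indirect measures are also the more exposed to bias. Latrine use, hand washing and pig keeping are both taught (Phase two) and scored (Pre-intervention examination). Participants who have just been taught may give the expected answers, and the assessor has sat in their sessions. The consequence is practical: under Ethical considerations, an intervention found effective will be considered for the district, and the outcome on which that is judged is not named.

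**Working it through.** **The plan's own figure.** Inputs from Study population: control prevalence 0.1464, intervention prevalence 0.1023, average 0.1244, z scores 1.96 and 0.84.

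n = (1.96 + 0.84)² × 2 × 0.1244 × 0.8756 / (0.1464 − 0.1023)² = 7.84 × 0.21785 / 0.0019448 = 878.2 pigs per group.

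This reproduces the stated 878.20, rounded to about 900. No figure needs correcting on this point.

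**How often the fallback could come into play.** With 900 per group and the same individual-level method, z = 0.0441 / √(0.21785/900) = 2.83, and 2.83 − 1.96 = 0.87, giving power of about 81%. Even if the full 30% reduction occurs, prevalence is therefore non-significant about 19% of the time, before any loss to the clustering that Statistical analysis recognises. With no effect, it fails to show a significant benefit 97.5% of the time.

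**Extra routes to the claim.** The protocol states no rule for combining outcomes, so what follows is an assumption: any one significant beneficial result suffices, tests are independent, and each is two-sided at 5% (2.5% in the beneficial direction).
- Prevalence alone: 2.5%.
- Prevalence or one combined score: 1 − 0.975² = 4.9%.
- Prevalence, perceptions or practices: 1 − 0.975³ = 7.3%.

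If perceptions and practices must both improve, independence gives 1 − 0.975 × (1 − 0.025²) = 2.6%, rising to 4.9% if the two scores always agree.

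**Observer bias.** Baseline measurement precedes allocation, since villages are grouped on their baseline prevalence before being randomised. Adjusting scores for baseline, as Statistical analysis plans, thus cannot remove bias that enters afterwards. For illustration, assume a bias of 0.2 standard deviations and no true effect. The chance of a significant score difference is Φ(0.2 × √(n/2) − 1.96), where n is the effective number per group:

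| n per group | Chance |
|---|---|
| 50 | 17% |
| 100 | 29% |
| 200 | 52% |
| 500 | 89% |

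Neither the bias nor n is in the protocol. As a guide, 900 pigs at the quoted 1.8 pigs per farmer is 500 farmers per group; clustering by village makes the effective number smaller, as does interviewing only five farmers per village in depth.

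**Whether practice must track transmission.** The Introduction says that carriers may persist for up to 25 years and eggs for over six months. Study limitations adds that housing pigs may need extra labour and food. Perceptions, and even some practices, can improve within two years without a matching fall in transmission.

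**The case against.** The strongest defence is that perceptions and practices are a pre-specified objective with their own analysis, that the sentence sits in a limitations section, and that it calls them intermediate outcomes. Nothing in the protocol drops the prevalence analysis or permits a null result to go unreported. All of that is right, and it confines the point to the inference drawn. It does not remove it, because the sentence says that these outcomes will be used to indicate reduced transmission.

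Some practices, such as latrine status and pig housing, are physical facts and less open to observer bias. The second assessment at the end of the study is less exposed to immediate recall. The budget lists an anthropologist to assist with data collection, so the researcher may not be the only assessor. For palpation, the Introduction quotes 100% specificity, which limits false positives, although missed cases remain possible. These points reduce the bias for part of the data. Interviews and hand washing remain exposed, and no masked assessor is specified.

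Stronger readings are tempting but unsupported:
- A reader might infer that the fallback applies only when prevalence does not fall. The text speaks of a significant reduction, so it covers any non-significant result, including a fall that is real but imprecisely estimated.
- A reader might count prevalence plus two scores at two times and quote 1 − 0.95⁵ = 23%. No passage sets an any-one-of-five rule, the figure counts results in the harmful direction, and repeated scores from the same households are unlikely to be independent.
- A reader might infer that someone else, such as the budgeted technician, should palpate after the intervention. The protocol does not show that this person would be blind to the village's arm, and changing the palpator between surveys would conflict with keeping methods similar.

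**Conclusion.** The concern holds as a fault in the stated rule of inference. As written, a non-significant main outcome can be followed by a claim of reduced transmission resting on outcomes that were taught and that are assessed by a researcher who cannot be blind to allocation.

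The size from multiplicity alone is modest: about 5% for two outcomes and 7% for three, against 2.5%, on the assumptions of independence and any one beneficial result sufficing. If both scores must improve, it may be barely above 2.5%. Observer bias is the larger threat, but its size is unknown and the figures for it are illustrations only. The conclusion does not depend on any of these numbers. It rests on the wording of Study limitations set against the main outcome in Study population and the researcher's roles in the two later sections. It does not follow that the prevalence analysis is abandoned or that the perception and practice outcomes are worthless.

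**What to change.** Replace the sentence in Study limitations. State that a claim of reduced transmission rests on the prevalence effect with its 95% confidence interval, whether or not it is significant. State that perceptions and practices (objective iii) are secondary outcomes that help to explain that result, and that their unblinded assessment is a limitation.

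Resolve the bracketed blinding note where this is cheap. Label the blood samples already planned with codes that hide village and arm, so that the antigen ELISA is read blind. Report it beside the lingual result as supportive only, because Study limitations itself describes antigen tests as still under trial, with antigen tending to disappear after about 200 days.

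Cost: a few lines of text and slight extra laboratory work for coding. The downside for the investigator is that a non-significant prevalence result must be reported as such, with its interval, and cannot be turned into a positive claim about transmission.
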